***Data analysis and power calculations***

Differences between groups will be analyzed by means of independent t-tests and Analysis of Covariance (continuous outcomes) or logistic regression (categorical outcomes). The power of the study is high. For instance, with a sample of 500 000 women we will be able to detect a 0.015 standard deviations (SDs) difference in BMI, gestational weight gain and self-reported health between migrant and non-migrant women with a power of 95 % (α=0.05). This corresponds to differences of 0.07 kg/m^2^ (assumed SD = 4.8), 0.06 kg (assumed SD = 4 kg) and 0.005 points (assumed SD = 0.3 points) in BMI, gestational weight gain and self-reported health respectively (15, 18). Given the large sample size we will also analyze GWG according to region of birth (6), economic status (low/middle/high) of birth country (7) and the combination between socioeconomic and migrant status.

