**Project description**

**Study design**

Data of exposures, outcomes and covariates (see below) will be retrieved from the Swedish Pregnancy Register for the years 2010 to 2018 and study will include approximately 500 000 women. An internal validation of this registry showed that variables within this registry has overall good to very good degree of coverage, agreement and internal validity (16).

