***Covariates and descriptive variables***

Following variables will be considered as confounders in the analysis and will also be utilized as descriptive data; maternal age, number of previous child labors, previous pregnancies in the Swedish Pregnancy Registry, number of born children in current pregnancy (i.e. single or multiple-pregnancy), length of pregnancy, county council, maternity care unit, smoking, alcohol consumption, type of delivery, infant sex, birth weight and date, stillbirth, dates for visits in maternity care and revisits after birth, educational attainment and occupation, estimated day of birth from ultrasound and last menstruation.

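### The named tests assume independent records, but no rule limits each woman to one pregnancy; if repeat pregnancies are kept, intervals for country of birth will be too narrow

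*Protocol*

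**What the plan says.** The protocol's section Data analysis and power calculations names the methods: "Differences between groups will be analyzed by means of independent t-tests and Analysis of Covariance (continuous outcomes) or logistic regression (categorical outcomes". It mentions no version of them for correlated records.

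Under Study design, the data are to be "retrieved from the Swedish Pregnancy Register for the years 2010 to 2018 and study will include approximately 500 000 women". No sentence restricts a woman to a single pregnancy within those nine years.

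The section Covariates and descriptive variables lists, among the confounders, "number of previous child labors, previous pregnancies in the Swedish Pregnancy Registry". These are two separate items: parity, and earlier pregnancies held in the same register. The rest of that list is largely at pregnancy level, for example length of pregnancy, infant sex and birth weight.

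The power statement again counts women: "with a sample of 500 000 women we will be able to detect". Its target is 0.015 SD for migrant versus non-migrant status on each of the three outcomes, with 95% power and α set at 0.05.

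**The concern.** Over nine years many women can be expected to give birth more than once. If each pregnancy is a row in the analysis, rows from the same woman are correlated, and an independent t-test, a standard ANCOVA or an ordinary logistic regression treats them as if they were not. Adding the number of earlier pregnancies as a covariate adjusts the mean. It does not remove the correlation between a woman's own records.

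The direction of the error depends on the exposure. Country of birth is the same in every pregnancy of a woman, so exposure and outcome are clustered together, and the naive standard error is too small whenever the outcome is positively correlated within a woman. Occupation, education and need of an interpreter can change between pregnancies, and ignoring the clustering can then make the standard error too small or too large.

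With about 500 000 records, large overall contrasts will hardly change. Interval width matters more in the smaller groups: the protocol plans gestational weight gain (GWG) analyses by region of birth, by economic status of the birth country, and by combined socioeconomic and migrant status.

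**Working it through.** **The plan's own figure.** Inputs: N = 500 000, difference 0.015 SD, α = 0.05 (two-sided assumed, since the protocol does not say), and a migrant share of 27% (Background and Significance; the power statement gives no split). The groups are then 135 000 and 365 000.

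- SE of the difference in SD units = √(1/365 000 + 1/135 000) = 0.00319.
- Power for 0.015 SD = Φ(0.015/0.00319 − 1.96) = 99.7%.
- Difference detectable with 95% power = (1.96 + 1.645) × 0.00319 = 0.0115 SD.

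The stated 95% is therefore not reproduced at a 27% share. It is on the cautious side and would match a migrant share of about 13%.

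**Effect of repeat pregnancies.** For an exposure that is constant within a woman, with m pregnancies per woman and within-woman correlation ρ:

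- design effect DE = 1 + (E[m²]/E[m] − 1) × ρ
- true SE / naive SE = √DE
- actual two-sided type I error = 2 × (1 − Φ(1.96/√DE))

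The protocol gives neither the distribution of m nor ρ, so both are assumed. The percentages are the shares of women with 1, 2 and 3 pregnancies, and the 500 000 are taken as pregnancies.

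| Split 1/2/3 | E[m] | E[m²]/E[m] | ρ | DE | SE ratio | Type I error | Power for 0.015 SD |
|---|---|---|---|---|---|---|---|
| 80/20/0 | 1.2 | 1.333 | 0.3 | 1.10 | 1.05 | 6.2% | 99.4% |
| 65/30/5 | 1.4 | 1.643 | 0.7 | 1.45 | 1.20 | 10.4% | 97.4% |
| 50/40/10 | 1.6 | 1.875 | 0.9 | 1.79 | 1.34 | 14.3% | 94.1% |

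For example, in the last row DE = 1 + 0.875 × 0.9 = 1.79, and the effective sample size is 500 000/1.79, about 280 000. In the first row it is about 455 000.

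**By outcome.** Take a 60/33/7 split. E[m] = 0.60 + 0.66 + 0.21 = 1.47, E[m²] = 0.60 + 1.32 + 0.63 = 2.55, and the ratio is 1.735.

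- GWG, ρ assumed 0.4 to 0.5: DE = 1 + 0.735 × 0.4 = 1.29 to 1 + 0.735 × 0.5 = 1.37. Standard errors are 14% to 17% larger and type I error is about 8% to 9%.
- BMI, ρ assumed 0.9: DE = 1 + 0.735 × 0.9 = 1.66. Standard errors are 29% larger and type I error is about 13%. The difference detectable with 95% power is 0.0115 × 1.289 = 0.0148 SD.

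**One pregnancy per woman.** Then E[m²]/E[m] = 1, DE = 1, and there is no error.

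**The case against.** The strongest reply is that the protocol describes its sample as women throughout and nowhere says that several pregnancies per woman will be analysed. The covariate shows that the register holds repeat pregnancies and that the extract can identify them. It could serve as a description, as a means of choosing one pregnancy per woman, or as a record of pregnancies registered before 2010. This stands in part: the consequence is conditional. It does not close the matter, because no selection rule is written, and the item is listed as a confounder. It would be zero for every woman if only first registered pregnancies were used.

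A second reply is that the variance estimator is commonly left to a statistical analysis plan, which may exist but is not shown, and that ANCOVA and logistic regression can be run with clustered errors. That is true of the two regressions. The independent t-test has no such option, and it is named in the protocol. The unit of analysis also determines what the 500 000 counts.

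Three stronger readings may tempt a reader, and the document supports none of them:

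- **That the power is overstated.** Even at a design effect of 1.66 the detectable difference is 0.0148 SD, within the 0.015 SD claimed. Over the whole assumed range power stays between 94.1% and 99.4%.
- **That the 13% error rate applies to the region-of-birth analyses.** The protocol plans these for GWG, where the same pregnancy split gives about 8% to 9%. The 13% belongs to BMI at an assumed correlation of 0.9.
- **That every interval would be too narrow.** This is certain in direction only for exposures fixed within a woman.

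**Conclusion.** The point holds in conditional form. The protocol commits to methods that in standard form need independent records, sets no limit of one pregnancy per woman, and lists a confounder that suggests repeat pregnancies are analysed, while it counts women. Followed as written, with repeats kept, intervals for country of birth and other exposures fixed within a woman would be too narrow. Nominal 95% intervals would cover about 94% to 86% (100% minus the type I errors of 6.2% and 14.3%).

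That size rests on assumed pregnancies per woman and assumed within-woman correlations. It also assumes that both are alike in the groups compared. It says nothing certain about occupation, education or interpreter need. It would be wrong to conclude that the results will be invalid: with one record per woman the problem disappears, and the power claim stands in either case. What is established is an undefined unit of analysis with a real consequence under one of its two readings. It should be settled before the data are extracted.

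**What to change.** In Study design and in Data analysis and power calculations, state whether the unit is the woman or the pregnancy, and which of the two the 500 000 counts. Then choose one of two routes.

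1. **One pregnancy per woman** by a fixed rule, for example the first in the register within the study years. The named methods can then stay. The cost is the dropped records.
2. **All pregnancies**, with GEE or cluster-robust standard errors by woman for both continuous and categorical outcomes. Replace the independent t-tests by the same clustered model without covariates. The cost is a change of model option and somewhat wider intervals.

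Both routes need a pseudonymous woman-level key in the extract. The section Ethical considerations and safety of participants describes the data as anonymous, so the key should be secured when the data are ordered. Without it, neither clustering by woman nor selecting one pregnancy per woman may be possible later. The power statement needs no new calculation beyond naming its unit.

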***Main exposure variables***

- Country of birth
- Need of an interpreter in contact with maternity care
- Educational attainment (corresponding to < 9 years, 9-12 years, > 12 years)
- Occupation (work, student, parental leave, unemployed, sick leave/disability pension, others)

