**Significance**

Migrant health represents a great public health priority and challenge (13, 14) and currently approximately 27 % of pregnant women in Sweden have migrant background (15). Pre-pregnancy body mass index and GWG is a modifiable risk factor for a wide range of pregnancy health outcomes including mortality and severe morbidity in both mother and child (1-4). Hence, this large population based registry study (n > 500 000) will provide novel data of weight status in early pregnancy, gestational weight gain and self-reported health in women with various socioeconomic and migrant background. A distinct study strength is the use of the Swedish Pregnancy Register which has is population-based and has good coverage (16). Furthermore, the large sample size will also allow us to provide data for GWG of migrant women stratified by geographical regions (6), economic status of birth country (7), as well as to examine whether inequalities in GWG can be attenuated by higher educational attainment or occupational status. All of this information is essential, even though the previous literature has demonstrated that migrant women have an increased risk for severe adverse pregnancy outcomes (5-7), less is known whether migrant women have an increased risk of unhealthy weight status, GWG and poor self-reported health.

Altogether, this project will provide evidence whether inequalities regarding weight status, gestational weight gain and self-reported health exist between women with migrant and non-migrant women and/or with low and high socioeconomic status. The data in this described project will therefore contribute to the existing literature. Furthermore, the study has also a great potential to aid in the development of appropriate clinical care and public health polices to promote the health of pregnant women with various socioeconomic and migrant backgrounds.

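### Economic status of birth country varies only between countries, so woman-level intervals for this GWG contrast are too narrow if it is read as an association with country economic status and compatriots are alike

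*Protocol*

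**What the plan says.** The section Data analysis and power calculations opens with the methods: "Differences between groups will be analyzed by means of independent t-tests and Analysis of Covariance (continuous outcomes) or logistic regression (categorical outcomes". It then gives a power statement for the migrant versus non-migrant comparison: "with a sample of 500 000 women we will be able to detect a 0.015 standard deviations (SDs) difference", "between migrant and non-migrant women with a power of 95 % (α=0.05". For GWG this is converted to "0.06 kg (assumed SD = 4 kg".

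The same paragraph adds the analysis at issue: "Given the large sample size we will also analyze GWG according to region of birth (6), economic status (low/middle/high) of birth country (7". No other method is named for it. The Significance section repeats the rationale ("the large sample size will also allow us to provide data for GWG of migrant women stratified by geographical regions (6") and continues with economic status of the birth country.

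"Country of birth" is listed under Main exposure variables, so it is available for every woman. It does not appear under Covariates and descriptive variables. The protocol mentions no random effect, cluster-robust variance or country-level analysis.

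**The concern.** All women born in one country share the same economic-status level, so the exposure varies only between countries. Adding women from countries already represented sharpens those countries' means, but it adds no new countries to a level. If women from the same country are at all alike in GWG, a level's mean is partly set by which countries happen to be in it, and one or two large countries can dominate. A woman-level test ignores that source of variation.

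No listed covariate handles this. Country of birth is not among them, and as a fixed effect it would absorb economic status entirely. The issue is also separate from repeat pregnancies: it remains with one pregnancy per woman, and clustering on the woman does not remove it.

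At stake is a statement that GWG differs by economic level of the birth country, with an interval that reflects tens of thousands of women when the comparison rests on a few dozen countries.

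**Working it through.** **The plan's own figure.** The unit conversion holds: 0.015 × 4 kg = 0.06 kg. The stated power does not reproduce exactly. With 27% migrants (Background; Significance) the split is 135 000 versus 365 000, and the SE in SD units is √(1/135 000 + 1/365 000) = 0.00319. Two-sided power for 0.015 SD is Φ(0.015/0.00319 − 1.96) = 99.7%, against the stated 95%. The stated figure is conservative. It concerns migrant versus non-migrant women only, so the mismatch does not bear on this point.

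**Inputs for the economic-status contrast**
- From the protocol: SD 4 kg; 27% of 500 000 = 135 000 migrant women.
- Assumed, because the protocol does not give them: three equal levels, so n = 45 000 women each; K = 20 or 50 countries per level; equal country sizes (CV 0) or unequal sizes (CV 1.3); ICC 0, 0.001 or 0.01.

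**Formulas** (variances in SD² units)
- Woman-level variance of a level mean: 1/n.
- Variance with country variation: ICC × (1 + CV²)/K + (1 − ICC)/n.
- r = ratio of the two standard errors for the difference between two levels.
- Actual error rate of a nominal two-sided 5% test with no true difference: 2 × [1 − Φ(1.96/r)].

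**Woman-level result.** SE = 4 × √(2/45 000) = 0.027 kg, so the 95% half-width is 0.052 kg whatever the ICC.

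**Worked example** (ICC 0.01, K = 50, equal sizes). Each level has 0.01/50 + 0.99/45 000 = 0.000222. The SE of the difference is 4 × √0.000444 = 0.084 kg, the half-width is 0.165 kg, and r = 0.084/0.027, or 3.16 before rounding.

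| ICC (between-country SD) | K per level | Sizes | r | Half-width, kg | Actual error rate |
|---|---|---|---|---|---|
| 0 | any | any | 1.0 | 0.052 | 0.05 |
| 0.001 (0.13 kg) | 50 | equal | 1.38 | 0.072 | 0.155 |
| 0.001 | 50 | unequal | 1.85 | 0.097 | 0.289 |
| 0.001 | 20 | equal | 1.80 | 0.094 | 0.277 |
| 0.001 | 20 | unequal | 2.66 | 0.139 | 0.460 |
| 0.01 (0.40 kg) | 50 | equal | 3.16 | 0.165 | 0.535 |
| 0.01 | 50 | unequal | 5.02 | 0.262 | 0.696 |
| 0.01 | 20 | equal | 4.85 | 0.253 | 0.686 |
| 0.01 | 20 | unequal | 7.84 | 0.410 | 0.803 |

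Between-country SD is 4 × √ICC.

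**How little heterogeneity matters.** With equal sizes the country term matches the woman term at about ICC = K/n. That is 20/45 000 = 0.0004 to 50/45 000 = 0.0011, or a between-country SD of about 0.08 to 0.13 kg. This is close to the 0.06 kg difference that the protocol treats as worth detecting elsewhere.

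**Simulation check.** With 4 000 runs per setting, log-normal country sizes and no true difference, the woman-level test rejected in 29% (K = 50) and 42% (K = 20) of runs at ICC 0.001, and in 67% and 78% at ICC 0.01. At ICC 0 it rejected in about 5%. A t-test on country means stayed between 4.6% and 5.6% throughout, including at higher ICCs.

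**The case against.** The strongest reply is that the protocol never claims an effect of country economic status. Neither the specific aims nor the hypothesis mentions it, and the Significance section speaks of providing stratified data and of inequalities between women. Read that way, the countries are fixed, the result describes women giving birth in Sweden, and a difference driven by one large country is a real difference in that population. Woman-level intervals are then defensible. This stands as a reading, and it makes the point conditional. It does not dispose of it: the aims speak of associations, the Significance section looks to clinical care and public health policy, and nothing limits the economic-status result to description.

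Second, the large-sample remark may only be a reason why migrants can be subdivided. The quantified power claim covers migrant versus non-migrant women alone. That is fair. But the number of women is still the only ground offered, and it does not secure precision for this contrast.

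Third, variance estimation for a secondary breakdown could sit in an analysis plan that is not shown, and clustered standard errors are compatible with the models named. This is true, but the protocol does name its methods for group differences, and they assume independent women.

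Fourth, the size depends on an ICC, country counts and level sizes that the documents do not give. This stands. A reader might infer that the test would be wrong most of the time: at ICC 0.05 the same formula gives intervals roughly 7 to 17 times too narrow. No ICC in the protocol supports choosing that value, and with 50 equal countries at ICC 0.001 the narrowing is only about 1.4-fold.

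A reader might also extend the criticism to region of birth. Region can be a plain label for groups of women, and stratified description by region is the most natural reading, so the case there is weak.

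**Conclusion.** The point holds conditionally. If the contrast is read as an association between birth-country economic status and GWG, the methods named give intervals that are too narrow whenever women from one country are alike. On the stated assumptions (45 000 women per level, SD 4 kg, 20 to 50 countries per level) the factor is about 1.4 to 2.7 at ICC 0.001 and about 3 to 8 at ICC 0.01. It is 1 at ICC 0, and the issue does not arise if the result is purely descriptive of these women.

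The documents do not support the conclusion that the main results are compromised. The migrant versus non-migrant, education and occupation contrasts were not the subject of this check, and the affected analysis is a secondary GWG breakdown. The change is worth making because the protocol leaves the inferential reading open and the data needed are already collected.

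**What to change.** - For contrasts between economic-status levels among foreign-born women, keep the planned ANCOVA or logistic model and use standard errors clustered on country of birth, with a few-cluster correction. This leaves the point estimate as the average over women.
- Add a country random intercept as a sensitivity analysis only, because it reweights countries. Weights are proportional to 1/[ICC + (1 − ICC)/m] for a country with m women. At ICC 0.01, a country with 100 women gets 0.0101/0.0199, about half the weight of one with 10 000, although it contributes one hundredth of the women.
- Report the number of birth countries and the largest country's share of women in each level.
- Do not cite the number of women as the basis for precision of this contrast.
- Present region-of-birth results, and any contrast left with woman-level intervals, as descriptive of the women in the register.

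The cost is a few sentences in the analysis section and wider, less favourable intervals for this secondary analysis. No new data are needed.

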**Ethical considerations and safety of participants**

Since the data in this study is collected retrospectively and anonymously, there are minimal risks with the study. The study may aid in promoting health of pregnant women with various socioeconomic and migrant backgrounds. Hence, we believe this study is ethically justified.

**Significance**

Migrant health represents a great public health priority and challenge (13, 14) and currently approximately 27 % of pregnant women in Sweden have migrant background (15). Pre-pregnancy body mass index and GWG is a modifiable risk factor for a wide range of pregnancy health outcomes including mortality and severe morbidity in both mother and child (1-4). Hence, this large population based registry study (n > 500 000) will provide novel data of weight status in early pregnancy, gestational weight gain and self-reported health in women with various socioeconomic and migrant background. A distinct study strength is the use of the Swedish Pregnancy Register which has is population-based and has good coverage (16). Furthermore, the large sample size will also allow us to provide data for GWG of migrant women stratified by geographical regions (6), economic status of birth country (7), as well as to examine whether inequalities in GWG can be attenuated by higher educational attainment or occupational status. All of this information is essential, even though the previous literature has demonstrated that migrant women have an increased risk for severe adverse pregnancy outcomes (5-7), less is known whether migrant women have an increased risk of unhealthy weight status, GWG and poor self-reported health.

Altogether, this project will provide evidence whether inequalities regarding weight status, gestational weight gain and self-reported health exist between women with migrant and non-migrant women and/or with low and high socioeconomic status. The data in this described project will therefore contribute to the existing literature. Furthermore, the study has also a great potential to aid in the development of appropriate clinical care and public health polices to promote the health of pregnant women with various socioeconomic and migrant backgrounds.

